## Methods: Monitoring

### Data Monitoring

Due to the low risk of this protocol, no data monitoring committee is required.

Should the intervention cause orbital myositis or other physical injuries in any of the participants, the research team, in consultation with the patient’s physician, will make the final decision to terminate the trial.

### Harms

Data collected with the eye tracker during assessments in the study will not give an immediate indication about participant risk. However, participant comfort and concern for their own health will be continuously monitored verbally by research personnel throughout the assessment. If the participant expresses concern all research procedures will stop and research personnel will call 911 with the participant’s consent. In case of such an adverse event the IRB will be immediately notified. The participants are required to have a caregiver/family member present during OFF-assessments. There will be an area on the physician clearance form (Supplementary Material Data Sheet 3 sample physician release form for PD) for instructions to minimize risk during the OFF-state as well as a schedule for the administration of medications before and after the OFF period. The medical waiver will include an additional area for any special instructions to research assistants as necessary. Patients that could be at significant risk for medical complications by withdrawing from medications will be excluded from the study.

### Auditing

The trial will be audited by compliance entities associated with the University of Illinois at Urbana–Champaign system.

## Discussion

Improvement in voluntary saccade function may occur due to changes at multiple levels of the saccade. Saccade improvements may occur due to increased eye muscle strength as well as better nervous system planning and control of saccades. Three sets of extraocular muscles are involved in performing saccades depending on their component composition (Sparks, 2002). The medial and lateral rectus muscles generate horizontal saccade movements (Sparks, 2002). The superior and inferior rectus muscles function with the superior and oblique muscle pairs for production of vertical saccade components (Sparks, 2002). Production of oblique saccades requires all three pairs of muscles to coordinate together (Sparks, 2002). Functional improvement of these muscles may impact the ability to perform movements of different horizontal and/or vertical components depending on which muscles are affected. At the nervous system level, communication between areas involved in the generation of saccades may increase to produce better coordination between the horizontal and vertical saccade systems. Control over peak saccadic velocity may also change as the training task aims to facilitate larger voluntary saccadic amplitudes, potentially inducing a change to the main sequence that has been seen previously in voluntary control of reflexive saccades (Muhammed et al., 2018).

The superior colliculus (SC) has been identified as a key area for target and timing selection for saccades in primates (Port and Wurtz, 2009). Neurons in the SC are thought to form a map of saccades by direction and amplitude, requiring the activity of a group of SC neurons to form a saccade of the correct amplitude and direction (Sparks, 2002). SC neurons receive cortical and subcortical input and communicate output to the midbrain and pontine areas, as well as all premotor areas associated with control of eye and head movements (Sparks, 2002). The cortical frontal eye fields – while not necessary for saccade initiation – contribute to saccade control, through activity mediated by the SC (Sparks, 2002). The cerebellum plays a key role by creating the error signal for saccades, which contributes to saccade accuracy, speed, and lack of variability (Robinson and Fuchs, 2001). This signal is also generated by different areas of the cerebellum depending on whether the saccade has a horizontal or vertical direction (Robinson and Fuchs, 2001). The posterior vermis and caudal fastigial nucleus generate horizontal saccade signals, while vertical saccade information is handled by the interpositus nucleus (Robinson and Fuchs, 2001). Through these signals, the cerebellum adds correction information to saccade commands prior to initiation of movement to achieve accurate saccades of the necessary speed (Robinson and Fuchs, 2001).

A lack of response to voluntary saccade training in the primary or secondary outcome measures would support the use of this protocol for testing saccades as part of a biomarker assessment for early detection and diagnosis of PD. An added dimension of biomarker potential may come from a differential response of the main sequence to the training between the two groups as measured by changes in characteristic peak velocity for given saccadic amplitudes. This would create a more robust saccade-based biomarker by adding a treatment-response dimension to the characterization suggested as a diagnostic tool by previous studies (Terao et al., 2013; Yerram et al., 2013; Termsarasab et al., 2015).

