## Abstract

**Background:** Voluntary saccade function gradually decreases during both the progression of Parkinson’s disease (PD) and neurologically healthy adult aging. Voluntary saccades display decreased length and increased saccade latency, duration, and the number of compensatory saccades in aging and PD. Saccades serve as the key eye movement for maintaining salient features of the visual environment on the high visual acuity fovea of the retina. Abnormal saccade behavior has been associated with freezing of gait in PD. We have not identified any studies that have investigated improvement in voluntary saccade function using voluntary saccade training.

**Objective:** We report an experimental protocol that tests a training paradigm following the principle of specificity to improve voluntary saccade velocity and amplitude, while decreasing latency and the number of compensatory saccades.

**Methods:** Persons with PD (n = 22) and persons with no known neurological disorders (n = 22) between the ages of 40 and 65 years will be recruited. In a randomized-block study design, all participants will perform voluntary saccades to targets in eight cardinal and intercardinal directions. In each of the eight sessions during the four-week intervention period, participants will train at three target amplitudes. Participants will perform 40 trials for each amplitude block, consisting of five randomly presented repetitions for each direction. Voluntary and reflexive saccades will be recorded pre- and post-intervention, along with clinical mobility assessment using the Movement Disorder Society Unified Parkinson’s Disease Rating Scale. Mobility scores, the amplitude, latency, and duration of the first saccade, and the number of saccades to reach the fixation target will be analyzed using an ANOVA of mixed effects.

**Discussion:** This protocol holds promise as a potential method to improve voluntary saccade function in persons with PD. Should persons with PD not improve on any outcome following the intervention, this lack of response may support the use of saccade assessment as a response biomarker for the diagnosis of PD.

**Trial Registration:** This protocol was retrospectively registered at ISRCTN (ISRCTN.com) since July 25, 2018. The first participant was recruited March 12, 2016. The protocol identifier is 17784042.

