One criticism against saccade measurements as a diagnostic tool for PD is that the abnormalities seen in saccadic movements tend to differ based on the experimental context (MacAskill and Anderson, 2016). Abnormalities in saccade latency and amplitude are known to occur in multiple neurodegenerative disorders, which could lessen biomarker specificity (MacAskill and Anderson, 2016). However, recent reviews outlined differential characteristics of saccadic performance in PD and several other neurodegenerative diseases (Termsarasab et al., 2015; MacAskill and Anderson, 2016). Additionally, research into the characteristic relationship between saccade duration, peak velocity, and amplitude has not been extensively undertaken in PD. This “main sequence” is believed to characteristically optimize the costs of speed and saccadic accuracy at a given amplitude (Bahill et al., 1975; Harris and Wolpert, 2006). If the main sequence relationship is affected by training differences in persons with PD compared to neurologically healthy persons, the biomarker potential for voluntary saccade training response would be further supported. One benefit of saccadic measurements as a PD biomarker is that assessments of eye tracking systems are non-invasive, unlike biochemical markers, which require blood or CSF extraction. Additionally, saccade testing could occur in a clinical setting without the need for physician supervision and biochemical testing facilities, with the most common side effect being possible fatigue from eye movement.

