### Trial Design

This trial is designed as a two-arm, pre-post, single center pilot trial with an equal number of participants with PD and participants with no known neurological disorders (control), which will be analyzed using an analysis of variance (ANOVA) with mixed effects.

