#### Secondary Outcome Measures

One secondary outcome for this study is Movement Disorder Society-sponsored new version of the Unified Parkinson’s Disease Rating Scale (MDS-UPDRS). The MDS-UPDRS assesses motor examination and complications, motor aspects of daily living, and non-motor aspects of daily living using a combination of questionnaire and task performance assessment (Goetz et al., 2008; Martinez-Martin et al., 2013). The MDS-UPDRS will only be assessed in participants with PD, as participants with no known neurological disorders should not present disability measurable with these instruments. Additionally, the peak saccadic velocity, duration, and amplitude will be analyzed as a measure of changes to the main sequence (Bahill et al., 1975).

Primary outcomes will be assessed by a member of the NDHD laboratory staff blinded to secondary outcome assessment, which will be performed on a separate day (see Table 5 for investigator team timeline). Secondary outcome assessors will be blinded to primary outcomes and will not be involved in training sessions. Changes after the four-week intervention from the initial value of each primary and secondary outcome measure will be analyzed using an ANOVA of mixed effects.

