#### Sample Size

There will be two groups with the same treatment: (1) a control group of participants with no known neurological disorders and (2) a test group comprised of participants with PD that have H&Y levels 1–2. In the absence of existing data in the literature to estimate the required same sample size for a protocol of this nature, the estimation is based on the number of eyes tested and trained in other eye movement studies and a 10% attrition rate seen in other studies performed by the authors (Hall et al., 2010; Knox and Wolohan, 2015; Ivanov et al., 2016; Heath et al., 2017).

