### Statistical Methods

After data cleaning is completed using the automatic and user-guided portions of the MATLAB program, the cleaned data for all trials, which contains pupil position data for both eyes, will undergo statistical analysis. Using SAS, an ANOVA with mixed effects will be performed using the finalized data concerning four variables of interest for both voluntary and reflexive saccades: (1) normalized mean velocity, (2) normalized angular distance, (3) latency for the first saccade in a trial, and (4) saccade count to target (SAS Institute Inc., Cary, NC, United States). For participants with PD, the UPDRS scores before and after the intervention will be included with the eight saccade variables in the ANOVA with mixed effects to determine if any significant clinical mobility improvements occur. In secondary analyses, saccade-related measurements will be compared between the voluntary and reflexive saccades and by target amplitude. In the case of non-normality, non-parametric statistical methods will be used. Saccade data that are not viable for statistical analysis due to problems in recording eye movements, such as blinks obscuring saccades and loss of fovea tracking during a saccade initiation or endpoint, will not be included in the statistical analyses. Main sequence analysis will be included as a secondary form of analysis. Due to the comparatively weaker relationship seen between peak velocity and amplitude in the range that will be recorded, analysis of the relationship between mean velocity and amplitude and the relationship between duration and amplitude will be included (Bahill et al., 1975).

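### The protocol reads an absent or differential group response as support for a PD diagnostic biomarker, but group comparisons against healthy adults do not show how well an individual's response identifies PD

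*Protocol article*

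**What the plan says.** The biomarker inference appears in several places and takes two routes.

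- **Absent response in PD.** The Secondary objectives propose that, if the improvements are absent in PD, saccade performance would be a potential early biomarker. The Abstract and Conclusion say that lack of response may support saccade assessment as a biomarker; the Abstract names diagnosis as the use, and the Conclusion names early detection and diagnosis. The Discussion makes the same inference with a firmer verb (would support).
- **Differential response.** The Discussion adds: "An added dimension of biomarker potential may come from a differential response of the main sequence to the training between the two groups". Its next sentence says this would make the biomarker more robust. Saccade Biomarker Potential makes a similar statement about training effects on the main sequence.

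On analysis, Secondary Outcome Measures says: "Changes after the four-week intervention from the initial value of each primary and secondary outcome measure will be analyzed using an ANOVA of mixed effects". For the primary variables, Statistical Methods says: "an ANOVA with mixed effects will be performed using the finalized data concerning four variables of interest". The same section plans a separate secondary analysis of the main sequence (mean velocity against amplitude, and duration against amplitude).

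On the comparison, Trial Design describes "an equal number of participants with PD and participants with no known neurological disorders (control"). Table 2 requires PD participants to meet diagnostic criteria, to be at Hoehn & Yahr stage 1–2 and to be on a stable PD regimen. It excludes comorbid neurological disorders. Saccade Biomarker Potential concedes: "Abnormalities in saccade latency and amplitude are known to occur in multiple neurodegenerative disorders, which could lessen biomarker specificity".

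**The concern.** A diagnostic biomarker has to tell one person with the disease from one person without it. A comparison of group means, or of group-level velocity–amplitude relationships, asks whether averages or curves differ. A group difference can be statistically secure while the two distributions of individual responses overlap heavily. The article moves from the group result to the diagnostic use without that step, and does so in a stated objective as well as in the Discussion.

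The sample limits the claim further. Saccade Biomarker Potential gives differentiation from other tremor disorders as a purpose and acknowledges overlap with other neurodegenerative diseases, yet no such patients are compared. Because all PD participants are already diagnosed, the data do not address detection before diagnosis either.

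If the stated inference is followed, a significant interaction, or a non-significant change in PD, could be published as diagnostic promise for a measure that separates even diagnosed PD from healthy adults poorly.

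**Working it through.** The article gives no effect size, SD, alpha, power, sensitivity or specificity, so there is no stated figure to reproduce. Under Sample Size, "the estimation is based on the number of eyes tested and trained in other eye movement studies". The check below illustrates what significance alone implies about individuals.

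**Inputs from the article**
- Recruitment of 22 per group (Abstract, Recruitment).
- A "10% attrition rate seen in other studies performed by the authors" (Sample Size): 22 × 0.9 = 19.8, so about 20 analysed per group.

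**Assumptions not in the article**
- Two-sided alpha of 0.05 (alternatives below).
- One change score per person, normal in each group with equal SD.
- A cut-off at the midpoint between the group means.

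**Step 1: smallest significant difference in SD units.** d = t(0.975, 2n−2) × √(2/n). For n = 20: 2.024 × √(2/20) = 2.024 × 0.316 = 0.640.

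**Step 2: individual separation at that difference.**
- Sensitivity = specificity = Φ(d/2) = Φ(0.320) = 62.6%.
- AUC = Φ(d/√2) = Φ(0.453) = 0.675.
- Hanley–McNeil SE = 0.085, so the 95% CI is 0.675 ± 1.96 × 0.085, about 0.51 to 0.84.

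**Step 3: dependence on the assumptions.**

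| Case | d | Sensitivity = specificity |
|---|---|---|
| n = 20, two-sided 0.05 | 0.640 | 62.6% |
| n = 22 (no attrition), two-sided 0.05 | 0.608 | 62.0% |
| n = 20, one-sided 0.05 | 0.533 | 60.5% |
| n = 20, two-sided 0.05/8 | 0.916 | 67.6% |
| n = 20, effect detectable with 80% power at two-sided 0.05 | 0.909 | 67.5% |

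**Step 4: what useful separation would need.** Solving Φ(d/2) = 0.80 gives d = 2 × 0.842 = 1.68. Solving for 0.90 gives d = 2.56. For a just-significant result at n = 20, the upper 95% limit for d is 1.27, or about 74% sensitivity and specificity, still short of 80%.

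**Step 5: the absent-response route.** With 20 people and a person-level change score, the 95% half-width for the mean change is t(0.975, 19)/√20 = 2.093/4.472 = 0.47 SD of change. Even an observed mean change of exactly zero is compatible with a true change of nearly half an SD in either direction. A non-significant change in PD therefore does not show absence of response, and it too says nothing about classifying individuals.

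**The case against.** Several counter-arguments carry weight.

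- **The main route is absent response, not a group difference.** This stands. The sentence about differential response is an extra argument, so the 63% illustration bears on that route only. Step 5 shows that the first route does not fill the gap.
- **ANOVA is not the only analysis.** This stands: a main-sequence analysis is also planned. It too describes relationships at group level.
- **The illustration is generic.** This stands in part. It would apply to any two-group study of this size and rests on assumptions the article does not state. It marks the significance threshold. A reader might take 63% as the accuracy to be expected from this trial, or conclude that the data could never support a diagnostic claim. The documents support neither reading: no effect size is given, and a much larger difference would separate the groups well.
- **No stand-alone classifier is proposed.** The Discussion speaks of one component of a biomarker assessment, adding a treatment-response dimension to existing saccade measures. That is fair, and it is a reason to set the response score beside the baseline score, since added value is the claim.
- **The trial is a pilot and much of the wording is hedged.** This is true and limits the weight of the point. However, the inference also stands in a stated objective, and the Discussion uses firmer verbs.
- **The specificity problem is disclosed.** The article also cites reviews describing saccadic features that differ between PD and other diseases, and argues that OFF-state testing makes the results more relevant to undiagnosed PD. A healthy comparator is a reasonable first step. Neither argument puts another disease group or undiagnosed people in the sample.
- **ROC detail may sit in an unseen analysis plan.** An absent ROC analysis would not by itself be a finding in a condensed article. The point is the inference the article does state.

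**Conclusion.** The point holds as a fault of inference: the article treats absent or differential group response as support for a biomarker for early detection and diagnosis, and the analyses it names do not address individual discrimination. The only contrast available is diagnosed early-stage PD against people with no known neurological disorder.

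At the significance threshold with about 20 per group, the implied AUC is about 0.68 (95% CI about 0.51 to 0.84), with about 63% sensitivity and specificity. Across the alpha choices tried, at 20 or 22 per group, sensitivity and specificity run from 60% to 68%. These values assume normal, equal-variance, person-level change scores and a midpoint cut-off. They show that significance alone is not enough; they do not predict the result. The primary comparison of training effects is unaffected.

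**What to change.** 1. For the biomarker objective, report the person-level AUC with 95% CI for the training-response score and for the baseline score, labelled exploratory. The baseline AUC shows whether four weeks of training add anything to a single saccade test.
2. State in advance that neither a significant group difference nor a non-significant change in PD is by itself biomarker support.
3. In the Abstract, Secondary objectives, Discussion and Conclusion, limit the conclusion to discrimination of diagnosed early-stage PD from healthy adults, and drop the references to early detection and diagnosis.

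Cross-validated sensitivity and specificity are optional: at this size they would be very imprecise (an observed 13 of 20 has an exact 95% CI of 41% to 85%).

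The cost is a short analysis of data already collected and some edits to wording, with no added participants, visits or measurements. The downside is wide intervals and a more modest claim.

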## Conclusion

This intervention holds significant promise as a low-cost, low resource-demand tool to improve motor functions of the eyes in persons with PD and adults with no known neurological disorders as well as mobility outcomes associated with eye function in persons with PD. Should persons with PD not show improvements on any metric following the intervention, a lack of response to voluntary saccade training may support saccade assessment as a biomarker for early detection and diagnosis of PD.

## Ethics and Dissemination

### Research Ethics Approval

All methods have been approved by the local IRB committee (see Table 8 for a full IRB revision history as of the publication of this article). All subjects will provide written informed consent (see Supplemental Materials Data Sheet 1 sample informed consent for informed consent form) in accordance with the Declaration of Helsinki. This protocol has been designed in accordance with SPIRIT guidelines for clinical trial protocols (see Table 9 for a summary of SPIRIT-required trial registration information).

**Table 8 T8:** IRB protocol revision chronology.

**Original Submission**	July 2, 2015	
Approval date	January 15, 2016	
Amendment 01	February 16, 2016	Update of research team list.
Amendment 02	October 3, 2016	Change in research location to Freer Hall room 250.
Amendment 03	July 31, 2017	Addition of testing in the off-medication state for participants with PD.
Amendment 04	April 9, 2018	Update of research team list.
Amendment 05	July 19, 2018	Medical release form specific to healthy controls added.

**Table 9 T9:** Trial registration data.

Primary registry and trial identifying number: 17784042
Date of registration in primary registry: July 25, 2018
Secondary identifying numbers: N/A
Source(s) of monetary or material support: Unfunded
Primary sponsor: University of Illinois at Urbana–Champaign
Secondary sponsor(s): None
Contact for public queries: [name], Ph.D., MA [contact]
Contact for scientific queries: [name], Ph.D., MA University of Illinois at Urbana–Champaign
Public title: Voluntary saccade training in persons with Parkinson’s disease and healthy adults
Scientific title: Voluntary saccade training in persons with Parkinson’s disease and healthy adults – two-arm, pre/post-trial
Countries of recruitment: United States of America
Health condition(s) or problem(s) studied: Parkinson’s disease, voluntary saccades, reflexive saccades
Intervention: Voluntary saccade training
Key inclusion and exclusion criteria: Ages eligible for study: ≥40 years; Sexes eligible for study: both; Accepts healthy volunteers: yes
Inclusion criteria: For participants with PD: (1) medically stable with diagnosis of PD by meeting the United Kingdom PD Society Brain Bank Criteria, (2) to have a Modified Hoehn & Yahr stage 1–2 (with unilateral involvement only, unilateral and axial involvement, and bilateral involvement without impairment of balance) in the conventionally defined OFF medication state, (3) to have medical clearance form from their physician for participation in the study, (4) to be in a stable regimen of PD medication 30 days prior to the initiation of the study and until the completion of the study, (5) to be willing and able to provide informed consent, (6) to be of age 40 and up, and (7) must have a caregiver/family member present for OFF-state assessment sessions.
For neurologically healthy participants: (1) no known neuromuscular disorders, (2) to have medical clearance form from their physician for participation in the study, (3) to be willing and able to provide informed consent, and 4) to be of age 40 and up.
Exclusion criteria: (1) presence of dementia based on The Montreal Cognitive Assessment (MOCA) –score of less than 25, (2) diagnosis of comorbid neurological disorder such as epilepsy, (3) history of neurological injury such as stroke, (4) history of brain surgery such as deep brain stimulation, (5) concurrent severe medical illness which in the opinion of the research team will preclude participation in the study (such illnesses may include but not limited to severe or uncontrolled cardiovascular disease, hypertension, pulmonary disease, or diabetes), (6) inability to attend and participate in at least seven of the training sessions, (7) uncorrected vision, history of retinal disease (e.g., macular degeneration), presence of optic neuropathy due to glaucoma or ischemic optic neuropathy, pseudoexfoliation syndrome, ocular surgery, ocular trauma, visually significant cataract, orbital myositis, blindness or refractive errors outside –5 to +3 D, (8) indication by the participant’s neurologist in the medical release form that testing the participant in the OFF-medication state would put PD participants at significant risk for medical complications.
Study type: Interventional
Allocation: no randomization; Intervention model: two-arm pre-post; Masking: non-masked
Primary purpose: eye movement training
Study Phase: Phase 0
Date of first enrolment: March 12, 2016
Target sample size: 44
Recruitment status: Recruiting
Primary outcome(s): For both voluntary and reflexive saccades: number of saccades needed to reach target amplitude, for first saccade: latency, normalized mean velocity, normalized amplitude
Key secondary outcomes: Unified Parkinson’s Disease Rating Scale

